### Data exclusion

All participants who complete the study will be included in the analysis, except as specified below. Data will not be imputed for the primary outcomes in this study. We will use sufficiently robust statistical models that accommodate missing data. Prior to the lab testing session (day 0), participants will be excluded if they have not adhered to at least five nights of the assigned sleep schedule and/or not adhered to the assigned sleep schedule for the two nights prior to the testing session. Participants are excluded from the study if they wake 30 min after their scheduled wake time on day 0. Participants are also excluded from the study if they do not follow the sleep schedule (or nap) following the lab session on day 0. For questionnaires assessing spontaneous cognition completed during PSG set-up on day 0, we may impute data for any missing responses using multiple imputation.

For the mind wandering task, for any given aim, participants will be included if they provide at least 1 day’s worth of data for that aim. We will exclude data where the participant has not understood the task or is not a conscientious responder (operationalized as below 50 per cent performance on both Go and NoGo trials). Participant understanding of the task will also be checked during a debrief at the end of the study. Timing of the mind wandering task is checked against sleep diary data, participant phone calls (regarding sleep and wake timing) and actigraphy data. If the task is completed more than 12 h post-wake time, data for that day will be excluded.

If participants report that they did not pay sufficient attention to the most graphic sections of either film and they are not observed to be watching the screen at least 80 per cent of the time, their data for the whole duration of the study will be excluded. For the intrusive memory diary, data will not be imputed. Only intrusive memories of the films are included. Unclear diary entries are discussed with participants during the debrief meeting at the end of the study. If the participant does not complete the intrusive memory diary for the entire duration of the study, their data will be excluded. We will not exclude participants who report a high number of intrusions, instead winzorization will be performed for outliers.

We will exclude data from the recognition memory task if the participant is not a conscientious responder. This is operationalized as below 50 per cent performance for both targets (images they have seen) and lures (images they have not seen).

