**Figure 1 f1:**
[figure not shown]
Timeline of study participation. During days −7 to −1, participants maintain a regular sleep schedule. Day 0 (lab session) is indicative of a participant with a habitual wake time of 8 am. Lab session timing depends on participant sleep schedule. All sessions are a maximum of 6 h long. For the night following the lab session, participants follow the regular sleep schedule. For the remaining four nights of sleep, participants sleep ad libitum. During days 1–5, participants complete a daily mind wandering task (sustained attention task), fill out a diary for intrusive memories, and repeat the recognition task on the final day.

Phase 2 is the lab session (day 0). Participants wake up 2 h prior to their habitual wake time. This is to ensure sufficient sleep during the nap and to mildly sleep-deprive the wake group. After reporting to the lab in the morning participants are set-up with polysomnography. Following this, they view an analog trauma film in a dark sound attenuated room. Participants are then randomly assigned to one of the two groups: an experimental (nap) group and a controlled (wake) group, for a 2-h period. During this time, those in the wake group can engage in specific activities provided by the researchers including coloring and puzzles. They are unable to use social media, watch videos, view photos, read, or engage in university study/other work during this time. At the end of this experimental period, polysomnography equipment is removed and there is a 30-min delay period for both groups, to allow for the effects of sleep inertia to subside for the nap group. Participants then complete a recognition memory task for images from the trauma film and a sustained attention task to measure mind wandering (hereinafter referred to as “mind wandering task”) in the same sound attenuated room. Following this, participants are provided with instructions for completing an intrusive memory diary.

Phase 3 includes the remaining 5 days of the experiment. Over the next five nights, we will continue to monitor participant sleep with diaries and actigraphy. Participants complete daily intrusive memory diaries, starting as soon as they leave the lab, with six entries at minimum. During each day, they complete the same mind-wandering task completed during the lab session. The recognition task is repeated on day 5. Following study completion, participants attend a debrief meeting.

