### Participants and recruitment

#### Sample size

Our target sample size is 114 participants, with 57 in each condition. This study is powered primarily on Hypothesis 1, the group effect (nap vs. wake) on intrusive memory frequency. Relevant effect sizes were derived from a variety of prior studies, which have also been reported within at least one of four meta-analyses. Previous studies [14, 15, 25] examining the effect of a nap compared to wake on intrusion frequency have detected small to medium effect sizes (Hedges’ *g* = 0.38 [26] and 0.69 [15]) for between-group differences in intrusive memory frequency in the days following the experimental manipulation. Gvozdanovic et al. (2023) [14] also found a nap led to significantly fewer intrusive memories than the wake group, however, an effect size was not provided. For studies examining recognition memory for the trauma film following overnight sleep compared to wake or partial sleep deprivation [13, 23, 40], we calculated a sample size weighted average for Cohen’s *d*, finding a medium effect size of 0.5 for between-group differences where sleep, relative to wake, led to improved recognition memory for the film. Consistent with these studies, to detect a medium effect size of 0.5, with a two-tailed α of 0.05 and 80 per cent power, 57 participants are needed per group (114 participants in total) [41].

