#### Sleep schedule adherence

The sleep schedule is set in collaboration with the participant based on self-reported habitual sleep schedule. Each night and morning of the study, participants call the study phone and leave a message to indicate sleep and wake times. Sleep diaries and participant phone calls are monitored daily by the researchers. Within the first three nights of participation, if it is clear that the participant’s sleep schedule is different than what was initially set, the sleep schedule is adjusted to match the participant’s actual sleep schedule, as long as it stills falls within the study criteria (they do not sleep before 22:00 or after 01:00 and do not wake before 06:00 or after 09:00). If the sleep schedule is adjusted, participant wake time on the day of the lab session is also adjusted (to 2 h prior to regular wake time), as is lab session timing. Based on sleep diaries and sleep/wake time phone calls, participants are excluded from the study if they do not adhere to the sleep schedule for at least five nights. Non-adherence includes napping, going to sleep too early, or oversleeping. Participants are also excluded from the study if they wake 30 min after their scheduled wake time on the day of the lab session. If a participant is non-adherent to the sleep schedule, participation is rescheduled if there is agreement that they will be able to adhere for the rescheduled week. After the lab session, the sleep schedule is followed for one more evening. If participants are non-adherent to the sleep schedule on this evening (eg, napping following the lab session), they are excluded from the study and cannot be rescheduled.

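### Excluding randomised participants who nap or break the sleep schedule after the nap/wake period can make the Hypothesis 1 analysis set depend on arm, and it discards usable Hypothesis 2a data

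*Protocol article*

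**What the plan says.** Randomisation takes place in the lab session on day 0, and participants learn their group immediately before the 2-h period (Randomization). The Data exclusion section then states: "Participants are also excluded from the study if they do not follow the sleep schedule (or nap) following the lab session on day 0". The Sleep schedule adherence section repeats the rule for the evening after the lab: "non-adherent to the sleep schedule on this evening (eg, napping following the lab session), they are excluded from the study and cannot be rescheduled". That section counts napping, early sleep and oversleeping as non-adherence.

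Under Study design, everyone wakes 2 h before their habitual time on day 0, and the reason given is: "This is to ensure sufficient sleep during the nap and to mildly sleep-deprive the wake group".

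The analysis set is study completers less the listed exclusions (Data exclusion). The Aim 1 model in Analytic strategies is a generalized linear mixed model with a participant random intercept, and sex and day as covariates. The article states no analysis of all randomised participants beside it.

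The Data exclusion section also has a diary rule, "If the participant does not complete the intrusive memory diary for the entire duration of the study, their data will be excluded", and a general statement on missing data, "We will use sufficiently robust statistical models that accommodate missing data".

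**The concern.** Napping or going to bed early after the session comes after randomisation, and allocation can influence it. The wake arm leaves the lab short of sleep by design, while the nap arm has had a chance to recover some. The same rule applied to both arms can therefore remove more people from one of them.

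The article's own premise is that sleep soon after the film affects intrusions, so selecting on sleep in those first hours may also select on the outcome. If both links hold, the retained groups no longer differ only by allocation, and the hypothesis on which the trial is primarily powered is exposed.

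Hypothesis 2a is affected for no gain. Recognition is tested in the lab after a 30-min delay, before the participant can nap at home or go to bed early.

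Because people are excluded from the study and not only from an analysis, their later diaries may never be collected. The as-randomised result for Hypothesis 1 might then be unrecoverable.

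**Working it through.** **The plan's own figure.** The Sample size section aims "to detect a medium effect size of 0.5" "with a two-tailed α of 0.05 and 80 per cent power", and gives 57 per group. This does not reproduce: those inputs need 63 per group (normal approximation) or 64 (t-test), and 57 per group has 75.4% power by the t-test. That is a separate matter. Here 57 serves only as the number retained per arm.

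**Inputs.** From the documents: 57 per arm, a standardised difference of 0.5 and two-sided alpha 0.05. Assumed, because the documents give no values: the exclusion fraction e in each arm, and the correlation ρ between exclusion propensity and intrusions.

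**Model.** Take a standard normal outcome and remove the top fraction e of the propensity in each arm. With c = Φ⁻¹(1 − e), the retained mean shifts by −ρ·φ(c)/(1 − e). The bias in nap minus wake is the nap shift minus the wake shift.

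**Worked case: 20% wake, 5% nap, ρ = 0.5.**
- Wake: c = 0.842, φ(c) = 0.280, shift = −0.5 × 0.280/0.80 = −0.175.
- Nap: c = 1.645, φ(c) = 0.103, shift = −0.5 × 0.103/0.95 = −0.054.
- Bias = −0.054 + 0.175 = +0.121 SD. A true difference of −0.50 appears as −0.38.
- With ρ = −0.5 the bias is −0.121 and the same difference appears as −0.62.
- Standard error = √(2/57) = 0.187. With no true effect the two-sided rejection rate is Φ(−1.96 − 0.121/0.187) + Φ(−1.96 + 0.121/0.187) = 0.099.

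A simulation of this case gave biases of −0.122 and +0.124, with type I error 0.095 and 0.112.

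**Range of assumed rates.**

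| Wake / nap excluded | Bias at ρ = ±0.3 (SD) | Bias at ρ = ±0.5 (SD) | Type I error at ρ = ±0.5 |
|---|---|---|---|
| 5% / 5% | 0 | 0 | 0.050 |
| 10% / 2% | ±0.044 | ±0.073 | 0.067 |
| 15% / 5% | ±0.050 | ±0.083 | 0.073 |
| 20% / 5% | ±0.072 | ±0.121 | 0.099 |
| 25% / 5% | ±0.095 | ±0.158 | 0.134 |

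At ρ = 0 the bias is zero for every pair of rates.

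**On a count scale.** Assume true means of 5 (wake) and 3 (nap), with excluded people having k times the intrusions of retained people. The retained mean is the overall mean/(1 − p + pk), where p is the fraction excluded. For p = 0.20 wake, 0.05 nap and k = 1.5: wake 5/1.10 = 4.55, nap 3/1.025 = 2.93, difference 1.62 instead of 2 (−19%). The wake-to-nap rate ratio changes by the factor 1.025/1.10 = 0.932 (−6.8%). For k = 2/3 the difference grows by 15% and the ratio by 5.4% (0.983/0.933). The apparent size therefore depends on the scale. If the Aim 1 model uses a log link, which the article does not state, the ratio is the relevant one.

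**The case against.** The rule has a purpose. A wake participant who naps that afternoon has in effect received some of the other condition, and a mechanistic study in healthy volunteers has reason to protect the contrast. By day 0 participants have also been selected for schedule adherence, so later breaches may be rare. No exclusion rate is given for either arm, and the count-scale shift is modest on a rate ratio. All of this stands. It supports reporting an adherent-set analysis, but not making it the only analysis.

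A reader might infer more than the documents support:

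- **That Hypothesis 1 is biased, or in a known direction.** The Study design section makes a higher wake-arm exclusion rate plausible, but nothing shows that it occurs or how it relates to intrusions.
- **That the diary rule removes anyone who misses a day and contradicts the missing-data statement.** The sentence can equally mean that no diary was completed at any point. That reading fits the missing-data statement, the at-least-one-day rule for the mind wandering task and the next-day contact after a missed diary. A loss of 17% to 26% (1 − 0.97⁶ = 16.7%, 1 − 0.95⁶ = 26.5%) needs the strict reading, assumed daily completion of 97% or 95%, and independent misses. Misses that cluster within people would lower it. What remains is an ambiguous wording.
- **That every listed exclusion has this fault.** The pre-lab and day 0 wake-time rules act before the manipulation, and the film-attention rule concerns viewing before participants know their group.

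**Conclusion.** The point holds for the exclusion after the lab session. The article fixes a whole-participant removal for behaviour that follows the randomised condition and can depend on it, and it states no as-randomised analysis. The rule's existence is certain. The size and sign of its effect are unknown. Under the assumed rates the bias reaches about 0.12 SD at 20% wake and 5% nap with a correlation of ±0.5, and about 0.16 SD at 25% and 5%. It is zero if exclusion is unrelated to intrusions, or if both rates and mechanism are the same in the two arms. For Hypothesis 2a the loss of recognition data already collected needs no such assumption: it follows directly whenever someone is excluded under this rule. The diary rule needs clearer wording only.

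**What to change.** - From now on, keep participants who nap or break the schedule after the lab session in diary follow-up.
- Analyse Hypothesis 1 in all randomised participants, as randomised, using the observed diary days in the planned mixed model.
- Analyse Hypothesis 2a in all randomised participants with lab recognition data.
- Present the schedule-adherent set alongside as a per-protocol analysis, with exclusions by arm.
- In Aim 3, remove only the affected night.
- For participants already excluded, use whatever data exist and say so. Their lab recognition scores were collected before exclusion, but their later diaries may not exist.
- State that the diary exclusion applies only to participants with no diary data, so that partial diaries contribute their observed days. Do not scale totals by days observed: that assumes a constant daily rate, while the Aim 1 model adjusts for day.

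The cost is a wording change in the protocol and preregistration, continued diary collection for the participants concerned, and some dilution of the contrast from those who slept off-protocol, which the per-protocol analysis will show. Because recruitment has been under way since mid-2024, full as-randomised recovery for Hypothesis 1 may no longer be possible, and an early change limits the loss.

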#### Recognition and mind wandering tasks

Following the 2-h sleep or wake opportunity, participants complete two tasks. The first is a recognition task. Participants view targets (images from the films) and lures (similar images never seen) and are required to judge whether they witnessed these during the film. The task includes 64 images in total and takes ~10–15 min to complete. Recognition memory task performance will be assessed with the discriminability index (*d-prime* = transformed hits rate − transformed false alarm rate). As a planned secondary analysis, performance on targets, and lures will be individually examined as findings in the literature are inconsistent as to whether performance on targets or lures is driving sleep-related effects on *d-prime* [13, 40].

Mind wandering or off-task thought is related to failures of attention on a range of different sustained attention tasks [64]. The mind wandering task in the current study is an adapted version of a sustained attention to response Go/NoGo task, which has previously been used to elicit and examine mind wandering [65]. Participants are instructed to pay attention to a series of digits and press a button for all digits except the digit 3. The presentation of stimuli is stopped at random times (every 30–70 s) to probe mental state (eg, on/off task) and vigilance of the participants with a series of questions, taking ~18–20 min to complete. The primary outcome from the mind wandering task is frequency of mind wandering.

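### The recognition-task exclusion rule removes only worse-than-chance responding and always keeps a participant who gives the same answer to every image

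*Protocol article*

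**What the plan says.** The protocol article states the purpose of the recognition rule under *Data exclusion*: "We will exclude data from the recognition memory task if the participant is not a conscientious responder". The criterion follows at once: "operationalized as below 50 per cent performance for both targets (images they have seen) and lures (images they have not seen". No other performance rule or check of understanding is given for this task.

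Under *Recognition and mind wandering tasks*, participants "are required to judge whether they witnessed these during the film", and "The task includes 64 images in total and takes ~10–15 min to complete". The split between targets and lures is not given. "Recognition memory task performance will be assessed with the discriminability index", defined as transformed hit rate minus transformed false-alarm rate. *Analytic strategies* uses this score, taken just after the nap or wake period, as the outcome of Hypothesis 2a and the mediator of Hypothesis 2b. The day 5 score is used in parallel exploratory analyses.

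The mind wandering task has a rule of the same form, "operationalized as below 50 per cent performance on both Go and NoGo trials". There the article also names failure to understand the task as a ground for exclusion, and adds: "Participant understanding of the task will also be checked during a debrief at the end of the study".

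**The concern.** A rule meant to catch careless responding should at least catch someone who presses one key from start to finish. Requiring failure on both image types does the opposite. A constant answer is necessarily perfect on one type and wholly wrong on the other, so it can never fail on both.

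Such a record carries no information about memory, yet it would enter Hypotheses 2a and 2b with d-prime near 0 whatever the Condition. If these records were equally common in both groups, they would shrink the group difference in d-prime and, where conscientious participants score above chance, widen its spread. The day 5 repeat is more exposed because it is done at home, which the *Discussion* acknowledges is less controlled than the laboratory.

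**Working it through.** The article gives no expected exclusion rate, so there is no stated figure to reproduce. The rule can be evaluated directly.

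**Inputs.** From the article: 64 images, and exclusion only if accuracy is below 50% on targets and also on lures. Assumed: a two-choice answer, and a 32/32 split where a split is needed, with other splits shown.

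**1. Constant responders (no split needed).**

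| Pattern | Targets | Lures | Below 50% on both? |
|---|---|---|---|
| Always seen | 100% | 0% | No, kept |
| Always not seen | 0% | 100% | No, kept |

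Hit and false-alarm rates are both 1 or both 0, so d-prime is near 0 after the usual correction for extreme rates.

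**2. Who is excluded.** Accuracy below 50% on targets means a hit rate below 0.5. Accuracy below 50% on lures means a false-alarm rate above 0.5. Together they force d-prime below 0. Only reversed responding is removed.

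**3. Guessers, for context.** For a participant who says seen with probability q whatever the image, with nT targets and nL lures:

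P(excluded) = P(Bin(nT, q) < nT/2) × P(Bin(nL, 1 − q) < nL/2)

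At 32/32 and q = 0.5, P(X ≤ 15) = 0.430, and 0.430² = 0.185. So 18.5% are excluded and 81.5% kept.

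| Split | q | Kept |
|---|---|---|
| 32/32 | 0.5 | 81.5% |
| 32/32 | 0.4 or 0.6 | 92.3% |
| 32/32 | 0.3 or 0.7 | 99.5% |
| 24/40 | 0.5 | 81.7% |
| 16/48 | 0.5 | 82.2% |
| 31/33 | 0.5 | 75.0% |

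Over all splits with at least 4 images of each type and all q, the highest exclusion probability is 32%.

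**4. A same-answer check.** 0.95 × 64 = 60.8, so the threshold is 61 identical answers. At 32/32, a record with 61 or more seen answers has at most 3 of 32 lures correct (9.4%), and the mirror case has at most 3 of 32 targets correct. A balanced guesser reaches 61 with probability 2 × (1 + 64 + 2,016 + 41,664) / 2^64 = 2 × 43,745 / 2^64, about 5 × 10⁻¹⁵. The check finds constant responders and leaves balanced guessers alone.

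**5. Go/NoGo.** Pressing on every digit gives 100% Go and 0% NoGo; never pressing gives 0% and 100%. The accuracy rule keeps both. With assumed counts from 200/25 to 800/100 Go/NoGo trials, random pressing at q = 0.5 is kept about 76% to 79% of the time.

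**6. Effect on Hypothesis 2a.** If a fraction f in each group are constant responders with d-prime 0, and the others have mean μ, SD σ and standardized effect δ, the effect becomes approximately

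δσ(1 − f) / √[(1 − f)σ² + f(1 − f)μ²]

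This is below δ for any f above 0. The article gives none of f, μ or σ, so the formula yields a direction and no size.

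**The case against.** Four points can be made for the plan.

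- **Guessers.** A reader might infer that keeping some 82% of balanced guessers is itself an error. The documents do not support that. Accuracy cannot separate a guesser from someone who remembers little, and excluding on accuracy would select on the Hypothesis 2a outcome. This objection stands, and it confines the point to constant responding.
- **Go/NoGo.** A reader might infer that the mind wandering rule fails just as badly. It has a separate ground for exclusion (not understanding the task) and a debrief, and the *Discussion* says task performance is monitored. The debrief has no numerical criterion and addresses understanding rather than carelessness, so it may catch some such records but not reliably all. The outcome is also frequency of mind wandering, not accuracy, and NoGo errors may be genuine lapses of attention. This largely stands.
- **Size.** A reader might infer a material loss of power. That would need a prevalence of constant responders and a d-prime distribution, and the article gives neither. The Hypothesis 2a task is done in the laboratory, and film attention is screened, so the prevalence may be low. The study is powered primarily on Hypothesis 1, which uses neither task. This stands.
- **Wording.** It might be said that either type was meant. Neither rule reads that way, and if it was meant the text would still need correcting.

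None of this answers the constant responder in the recognition task, for which no other check is stated.

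**Conclusion.** The point holds for the recognition task. As written, the rule excludes none of the participants who give one answer throughout. That conclusion follows from the wording alone and does not depend on the target/lure split. The rule removes only records with negative d-prime, so it misses the plainest form of the behaviour it is meant to screen out, in data that form the Hypothesis 2a outcome, the Hypothesis 2b mediator and the day 5 exploratory repeat.

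The guessing figures rest on the assumed two-choice format and, for 81.5%, on a 32/32 split; they describe the rule and are not a defect in themselves. For Go/NoGo the finding is limited to a gap worth a sensitivity analysis. Any attenuation of the nap effect on d-prime has a known direction if constant responders are equally common in both groups and the others score above chance on average, but its size is unknown. The primary analysis of Hypothesis 1 is untouched.

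**What to change.** **Recognition task.** Keep the current rule, since it catches reversed responders. Add that a recognition record is also excluded if at least 95% of its 64 responses are the same (61 or more), judged blind to Condition. Report Hypothesis 2a and the day 5 analysis with and without the exclusions. Do not change the rule to below 50% on either type: at 32/32 that would also remove 67.5% of balanced guessers by accuracy, and so select on the outcome.

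**Mind wandering task.** Leave the exclusion rule as it is. Flag always-press and never-press records and run the Hypothesis 3a and 3b models with and without them. Do not exclude on NoGo errors.

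**Cost.** A few sentences, settled before the final analysis begins, and an extra sensitivity run. A few more recognition records may be excluded.
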